### Secondary outcomes

2.7

Incidence of Gastrointestinal bleeding consequent upon aspirin therapy (major and minor bleeding).

Gastrointestinal bleeding is classified as major bleeding: 2 g loss of hemoglobin or requirement of hospitalization; Minor bleeding: any bleeding less severe than above.^[22]^

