### Study design and settings

2.1

This is an open-label, two-arms, parallel, non-randomized (consecutive patients’ randomization) proof of concept, phase 4 pharmacokinetic/ pharmacodynamic study. We will recruit eligible patients from the stroke unit of designated recruitment centers (Hamad General Hospital). Patients who satisfy pre-specified inclusion criteria will be invited to participate in the study. Patients who agreed to take part will be screened, counseled, and enrolled in the study. They will be required to sign a consent form before allocation. This study was approved by the local MRC and The Institutional Review Board (IRB) (Hamad Medical Corporation, **MRC number: 01–18–156**) and registered in clinicaltrials.gov (NCT04330872) (Fig. 1).

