### Randomization, allocation concealment, and blinding

2.3

Consecutive patients meeting the eligibility criteria will be explained about the study procedures by one of the trial investigators following that that patient will be consented by designated study investigators (Supplementary materials 1. Consent form). If the patient consents to participate in our trial, then he/she will be allocated to either plain or EC aspirin arms following their admission order. Outcome assessors and data analysts are blinded to patient allocation.

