### Interventions

2.4

Once allocated to one of the two study arms, the study participants will be administered the study medication as either enteric-coated or plain Aspirin on day 1. Patients assigned will be prescribed plain loading dose (Dispersible 300 mg stat followed by Aspirin 75 mg tablets, Actavis UK Ltd) or EC Aspirin loading dose (300 mg stat followed by100 mg, Bayer, Germany) for 3 days (study duration). Irrespective of the design of the study, all patients enrolled in the study will receive other standards of care management according to HMC ischemic stroke guidelines. Patients will be required to give blood samples (10 mL) for estimation of the TXB2 level at baseline and on day 3, which marks the end of the study. Blood samples will be taken as part of the patient's routine investigation/care by the phlebotomist. Study samples will be taken by a designated study investigator as per standard protocols consistent with HMC guidelines. Study samples will be kept in labeled with anonymous patient-specific identifiers and kept in study refrigerators until completely used. Patients will be kept on other treatments constituting the usual standards of care management for established ischemic stroke, and this will be maintained throughout the study. We anticipate that it would take about one month to complete patient recruitment. Following the end of the study, laboratory analysis of biological samples will be carried out within 3 weeks with subsequent data evaluation and analysis.

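### The only safety outcome counts gastrointestinal bleeding under a causal condition with no stated criterion; as both arms take aspirin, the condition can only remove events

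*Protocol article*

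**What the plan says.** Section 2.7 (Secondary outcomes) lists one outcome: "Incidence of Gastrointestinal bleeding consequent upon aspirin therapy (major and minor bleeding". The sentence that follows grades the bleeds: "Gastrointestinal bleeding is classified as major bleeding: 2 g loss of hemoglobin or requirement of hospitalization; Minor bleeding: any bleeding less severe than above". That grading uses severity only; it contains no test of causation.

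Four other statements bear on the point:

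- **Design (section 2.1):** "This is an open-label, two-arms, parallel, non-randomized".
- **Masking (section 2.3):** "Outcome assessors and data analysts are blinded to patient allocation".
- **Treatment (section 2.4):** "the study participants will be administered the study medication as either enteric-coated or plain Aspirin on day 1". No arm is without aspirin.
- **Duration (section 2.4):** treatment is given "for 3 days (study duration".

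The article does not say what makes a bleed a consequence of aspirin, or who decides.

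**The concern.** Taken at its word, the outcome needs two things: a GI bleed, and a causal link from aspirin to that bleed. The comparison is between two formulations of aspirin, so relation to aspirin does not distinguish them. The difference of interest would show in a count of all GI bleeds. A second condition adds nothing to that comparison and makes each count depend on a judgement.

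Two things are at stake. First, the absolute incidence in each arm is too low by whatever share of bleeds is not attributed. Second, if that share differs between the arms, the comparison is distorted. Unequal shares are conceivable because the study is open-label. The article does not say that ward staff or investigators, who may be the first to record or interpret a bleed, are kept unaware of the formulation.

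**Working it through.** The plan gives no figure for bleeding, so there is none to reproduce. Its sample size in section 2.8.1 is justified by a difference in means and is not tied to this outcome.

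**Inputs**

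- Patients per arm: 21, total 42 (sections 2.8.1 and 2.2).
- True GI bleed risk over the study, *p*: not given. Assumed equal in both arms, range 1% to 10%.
- Share of bleeds attributed to aspirin, *a*: not given. Assumed range 50% to 100%.

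**Step 1. Weight of one bleed.** 1/21 = 4.8 percentage points of an arm's incidence. This holds for any yes/no outcome with 21 per arm; it shows only how much one attribution decision can matter.

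**Step 2. How many bleeds to expect.** Expected bleeds per arm = 21 × *p*. Chance of no bleed in the whole study = (1 − *p*)^42.

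| Assumed *p* | Expected bleeds per arm | Chance of none in 42 |
|---|---|---|
| 1% | 0.21 | 0.656 |
| 5% | 1.05 | 0.116 |
| 10% | 2.10 | 0.012 |

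**Step 3. Condition applied equally.** Counted incidence = *p* × *a*, and the ratio between arms = *a*/*a* = 1.0. With *p* = 5% and *a* = 80% in both arms, the counted incidence is 0.05 × 0.80 = 4.0%, and the expected count per arm falls from 1.05 to 0.84. The comparison is sound and the absolute incidence is one fifth too low.

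**Step 4. Condition applied unequally.** With equal true risks, the apparent ratio is the ratio of the attributed shares, whatever *p* is. The apparent risk difference is *p* × (*a*₁ − *a*₂).

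| Attributed shares | Apparent ratio | Risk difference, *p* = 1% | *p* = 5% | *p* = 10% |
|---|---|---|---|---|
| 90% v 60% | 1.5 | 0.3 points | 1.5 points | 3.0 points |
| 100% v 50% | 2.0 | 0.5 points | 2.5 points | 5.0 points |

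In bleeds per 21 patients, the largest of these is 21 × 0.05 = 1.05 and the smallest is 21 × 0.003 = 0.06. Over the assumed range, the expected distortion is about one bleed at most.

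**Step 5. All GI bleeds counted.** *a* = 100% in both arms, so the ratio is 1.0 by construction and the incidence is not understated.

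**The case against.** The strongest reply has four parts.

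1. **The phrase may be loose.** It could mean no more than bleeding while on aspirin. The outcome section describes no attribution step, and the grading sentence has no causal test. This reading is possible, and under it nothing is lost. The words are nonetheless causal, and if the looser meaning is intended the text should say so.
2. **Assessors are blinded.** If they apply the condition, attribution should not differ by arm. This stands, and it largely closes the route to a biased comparison in that case. A reader might infer that assessors see only bleeds already recorded as aspirin-related, so that blinding comes too late. The documents do not say that. Recording is governed by a case record form placed in a supplement that is not shown. Nor does the article say that the assessors decide causation, so the route is not shown to be closed either.
3. **Detail is left to the full protocol.** Who judges relatedness, and how, is commonly left out of an article, and that omission alone would be no finding. The point here concerns what the article does fix: an outcome definition with a condition that cannot help the comparison.
4. **Few events.** With 42 patients over three days, few bleeds are likely. This stands and limits the importance of the point.

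A reader might also take the minor class, "Minor bleeding: any bleeding less severe than above", to admit bleeding from any site. The subject of the full sentence is gastrointestinal bleeding, and major and minor are classes within it, so that reading is not supported.

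**Conclusion.** The point holds as an avoidable weakness in the definition of the only safety outcome. A causal condition with no stated criterion is attached to an outcome in a study where everyone takes aspirin. It can lower the counts but cannot make the comparison more informative.

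The certain part is limited: if the condition is applied equally, absolute incidence is understated by the unattributed share and the ratio is intact. Bias between arms is a possibility only. It requires unblinded staff to influence attribution, and to do so differently by arm. A reader might infer that the bias would favour the enteric-coated product, on the idea that coating is thought to protect the stomach. Nothing in the article shows such a belief or its effect, so no direction should be claimed.

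The sizes rest on an assumed bleed risk of 1% to 10% and attributed shares of 50% to 100%. Within those ranges the expected distortion is at most about one bleed per arm. The outcome is secondary and the primary outcome is a laboratory measure, so this is an inexpensive improvement and does not threaten the main result.

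**What to change.** Redefine the secondary outcome in section 2.7 as any gastrointestinal bleeding from the first study dose to the end of the study on day 3, irrespective of its judged relation to aspirin. State that the blinded outcome assessors grade each bleed as major or minor. If relatedness is of interest, record it for each bleed as a descriptive item that does not decide whether the bleed is counted.

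The cost is one reworded definition and, if needed, one line on the case record form. No extra patients, procedures or samples are required. The downside is that bleeds unrelated to aspirin are also counted, so the reported incidence may be slightly higher.

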### Setting and participants

2.2

Patients (male and female) (N = 42) with newly diagnosed ischemic stroke who are just to start aspirin therapy, and who attend stroke units of designated recruitment centers (Hamad General Hospital). We will enroll participants meeting the following inclusion criteria:

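### The hospitalization criterion for major gastrointestinal bleeding does not discriminate in patients who are already admitted to a stroke unit

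*Protocol article*

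**What the plan says.** Section 2.7 of the protocol article gives one secondary outcome: "Incidence of Gastrointestinal bleeding consequent upon aspirin therapy (major and minor bleeding". It then fixes the grading. A bleed is major if it meets either of two criteria, and everything else is minor: "2 g loss of hemoglobin or requirement of hospitalization; Minor bleeding: any bleeding less severe than above". The definition is cited to an outside source that is not at hand.

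Three other places in the article describe who is graded and for how long:

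- Section 2.1, on setting: "We will recruit eligible patients from the stroke unit".
- Section 2.3, on allocation: patients are "allocated to either plain or EC aspirin arms following their admission order". The same section states that those who assess outcomes and those who analyze the data do not know the arm.
- Section 2.4, on follow-up: blood for TXB2 is drawn "at baseline and on day 3, which marks the end of the study".

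Section 2.2 gives the size: "Patients (male and female) (N = 42) with newly diagnosed ischemic stroke".

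**The concern.** A need for hospital care can mark a serious bleed only among people who are not already in hospital. Here the stroke, not the bleed, has put every participant there before the first study dose. One of the two routes to a major grade therefore does not fit the population described in the same article.

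At stake is how the only stated secondary outcome is graded. Two assessors who both follow the text could grade the same bleed differently. A bleed that needs active treatment but does not lower hemoglobin by the stated amount within three days could be placed with trivial ones. Blinding does not cure this, because the ambiguity lies in the rule and not in knowledge of the arm.

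**Working it through.** **Inputs.** The definition (section 2.7), the setting (2.1), allocation by admission order (2.3), end of study on day 3 (2.4), 42 patients (2.2) and 21 per arm (2.8.1). The article gives no bleeding rate, so the rates below are assumptions. It also gives no figure for bleeding that could be reproduced.

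**Step 1: apply the rule to three kinds of bleed under each reading of the hospitalization criterion.**

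| Bleed in an admitted patient | Literal: the patient requires hospital | Causal: the bleed brings about a new admission |
|---|---|---|
| Trivial, no relevant hemoglobin fall | major | minor |
| Serious, hemoglobin fall below the threshold by day 3 | major | minor |
| Hemoglobin fall at or above the threshold | major | major |

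On the literal reading all three rows are major and the minor category is empty. On the causal reading only the hemoglobin criterion acts. On neither reading are the first and second rows told apart, and that is the distinction the hospitalization criterion would have to supply.

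**Step 2: how many bleeds could be affected.** Expected bleeds = 42 × risk, and the chance of none = (1 − risk)^42.

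| Assumed 3-day risk, both arms | Expected bleeds | Chance of no bleed |
|---|---|---|
| 1% | 42 × 0.01 = 0.42 | 0.99^42 = 0.656 |
| 2% | 42 × 0.02 = 0.84 | 0.98^42 = 0.428 |
| 5% | 42 × 0.05 = 2.1 | 0.95^42 = 0.116 |

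At 1% to 2% the wording would on average touch less than one event. Only some of those bleeds would fall in the rows where the readings disagree.

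**Step 3: what a count can say.** The exact two-sided 95% upper limit for zero events in n patients is 1 − 0.025^(1/n). For n = 21 this is 1 − 0.025^(1/21) = 0.161, and for n = 42 it is 1 − 0.025^(1/42) = 0.084. With no bleed in one arm, two-sided Fisher p falls below 0.05 only at 5/21 in the other (0 vs 4: p = 0.107; 0 vs 5: p = 0.048). These figures bear on how counts are read. They say nothing about misgrading.

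**The case against.** The best defense is that the rule classifies bleeds and not patients. A trivial bleed in someone admitted for stroke does not itself require a hospital bed, so grading every bleed as major is a strained reading. That is fair, and the causal reading is the more natural one. It leaves the criterion almost idle, however, and does not rescue the serious bleed without the hemoglobin fall. A sensible assessor might instead ask whether the bleed would have needed admission had the patient been at home. That would discriminate, but it is a hypothetical judgment that the text does not state.

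A reader might also infer more than the documents support:

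- **That the major/minor split cannot work at all.** The two criteria are alternatives, and the hemoglobin criterion still separates major from minor on the causal reading. The split is narrowed, not broken.
- **That the trial fails because it cannot compare bleeding between arms.** Section 2.8.1 powers only a difference in means, section 2.8.3 names no test for bleeding incidence, and section 2.1 presents a proof-of-concept study. No powered or confirmatory bleeding comparison is promised, and the discussion foreshadows no claim of equal gastrointestinal safety.
- **That open-label treatment biases the grading.** Section 2.3 blinds outcome assessors. Ward staff may know the arm, which could affect whether minor bleeds are noticed, but that is separate from the grading rule.
- **That the missing volume unit is a defect in its own right.** It is editorial. Most readers would supply g/dL.

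**Conclusion.** The point holds in a limited form. The hospitalization criterion, as worded, does not discriminate in the population and time frame that the article describes. On the more natural reading the grading rests on hemoglobin alone, and a serious bleed without that fall is graded minor. This is a stated rule that fits its own setting badly, not a detail left to another document.

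Severity is minor. The rule concerns one secondary outcome, probably affects less than one event at assumed risks of 1% to 2%, and leaves the TXB2 primary outcome alone.

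The conclusion assumes that patients are inpatients when allocated, which the stroke unit and admission-order wording supports. That they stay in hospital through day 3 is inferred and not stated. If some were discharged earlier, a new admission would become possible for them, but only within the few days left.

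**What to change.** In section 2.7, replace the hospitalization criterion with one that suits inpatients and can be judged by day 3, for example bleeding that leads to transfusion, endoscopic or surgical intervention, or transfer to a higher level of care. Prolonged stay is less suitable, since it generally cannot be judged when the study ends on day 3.

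State the hemoglobin criterion as a fall of 2 g/dL from a baseline hemoglobin value, and say which value is the baseline, because section 2.4 describes the study samples as taken for TXB2. Have the already blinded outcome assessor apply the rule. Read the resulting counts as descriptive.

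The cost is a change of outcome wording and matching entries on the case record form, including the hemoglobin values if they are not already captured there. The small downside is that the definition is no longer identical to the cited one, which the text should say.

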### Statistical consideration

2.8

#### Sample size

2.8.1

There are no previous studies to allow for a robust estimation of the study sample size. However, given that this is proof of concept study, we estimated that a sample size of 21 patients in each arm of the study would yield an approximate 80% power to detect 50% difference in population mean, for two-sided significance and an alpha level of 0.05.

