### Primary outcomes

2.6

Incidence of Aspirin non-responders at day 3 (level of residual serum TXB2 associated with elevated thrombotic risk (<99.0% inhibition or TXB2 >3.1 ng/mL).

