## Discussion

3

Our study is the third study assessing the possible effect of enteric-coated aspirin formulation on TXB2 inhibition. The first study was in 2006 by Cox et al. In their study of seventy-one healthy volunteers taking both Plain and EC aspirin in a randomized crossover design, they concluded that EC aspirin was not as effective as plain Aspirin in terms of TXB2 inhibition. The second study was in 2017 by Bhatt et al. It examined 40 diabetic patients in a randomized crossover design. Again, it concluded the inferiority of EC aspirin formulations compared to plain Aspirin (High proportion of incomplete TXB2 inhibition).

The findings from the previously mentioned trials prompted us to perform the first trial (up to the best of our knowledge), examining the level of TXB2 inhibition in stroke patients taking various formulations of Aspirin (plain vs EC aspirin). If a difference is TXB2 is found in our trial, this significant finding will invite additional clinical trials exploring the efficacy of various formulations of Aspirin measured via hard clinical outcomes such as major adverse cardiovascular events (MACE).

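### The 80% power is stated for an unnamed mean, but the primary outcome is a proportion of non-responders, so power for the primary comparison is not established

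*Protocol article*

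**What the plan says.** Under Primary outcomes the protocol article lists one item: "Incidence of Aspirin non-responders at day 3". A patient counts as a non-responder if TXB2 inhibition is below 99.0% or residual TXB2 exceeds 3.1 ng/mL. Each patient is thus classed yes or no, and the arms are compared on two proportions.

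Under Sample size, the article says that 21 patients per arm "would yield an approximate 80% power to detect 50% difference in population mean", two-sided, alpha 0.05. The variable is not named. No reference mean, SD, coefficient of variation (CV) or non-responder rate is given, and the text does not say whether the 50% is relative or absolute. The section opens with a caveat: "There are no previous studies to allow for a robust estimation of the study sample size". The total of 42 under Setting and participants agrees with 21 per arm.

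Under Statistical analysis, the methods named are the Wilcoxon signed rank test, Student's t test, repeated measures ANOVA, Spearman correlation and linear regression. None of these is a test of two proportions.

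**The concern.** A power figure applies only to the endpoint and effect it was calculated for. The article's single figure is for a mean, while its single primary outcome is a proportion. Loose wording is an unlikely explanation, because the named between-group methods are also for continuous data. The sizing and the analysis seem to have been framed around TXB2 as a measurement, and the primary outcome around a cut-point.

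What is at stake is how the result is read. A reader who takes the 80% as belonging to the primary outcome may treat a non-significant difference in non-responders as good evidence against an important one. Whether that is justified depends on rates that the article does not state.

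**Working it through.** **Inputs from the article:** 21 per arm (42 in total), two-sided alpha 0.05, power about 80%, a 50% difference in a mean, binary primary outcome. **Not given, so assumed over a range below:** CV and non-responder rates.

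**1. Can the stated 80% be reproduced?** For two means, the standardised difference detectable with 80% power is

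d = (z0.975 + z0.80) × √(2/n) = (1.960 + 0.842) × √(2/21) = 0.865.

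With the t distribution it is 0.886. Without an SD, 50% of a mean cannot be turned into d, so the 80% can be neither confirmed nor refuted. It depends on the reading:

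- *Half the reference mean, untransformed, equal SDs:* d = 0.5/CV, so 80% power needs a CV of at most 0.5/0.886 = 0.56 (t test) or 0.5/0.865 = 0.58 (normal). Power by t test is 89% at CV 0.5, 62% at CV 0.7 and 35% at CV 1.0.
- *Halving on the log scale:* the log SD may be up to ln 2/0.865 = 0.693/0.865 = 0.80. Power (normal) is 83% at CV 0.9 and 77% at CV 1.0.
- *Half an SD:* power is 37% (normal), and 63 per arm would be needed.

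A suitable SD would make the figure correct for a mean. It still would not be power for the primary outcome.

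**2. Power for the primary outcome.** Exact power at 21 v 21 is the sum, over all 22 × 22 possible pairs of counts (a, b), of

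Bin(a; 21, p1) × Bin(b; 21, p2), counting only pairs where the test is significant at two-sided 5%.

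| Assumed non-responder rates | Fisher exact | Uncorrected chi-square |
|---|---|---|
| 10% v 20% | 8% | 15% |
| 20% v 40% | 19% | 31% |
| 25% v 50% | 26% | 40% |
| 30% v 60% | 36% | 50% |
| 40% v 80% | 65% | 78% |
| 45% v 90% | 85% | 92% |
| 25% v 75% | 86% | 92% |
| 10% v 60% | 91% | 96% |

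The first six rows read the 50% as a relative halving. The last two read it as 50 percentage points.

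**3. Difference detectable with 80% power (Fisher exact).**

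| Lower rate | Higher rate needed | Gap (points) |
|---|---|---|
| 5% | 42.6% | 37.6 |
| 10% | 52.1% | 42.1 |
| 15% | 60.1% | 45.1 |
| 20% | 66.5% | 46.5 |
| 25% | 72.0% | 47.0 |
| 30% | 76.9% | 46.9 |

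By the pooled normal approximation the gaps are a few points smaller: 48.2% against 10%, 61.3% against 20% and 72.0% against 30%, which is 38 to 42 points.

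**The case against.** The best defence is that this is labelled a proof-of-concept study, calls its power approximate, and openly admits that it lacks a firm basis for sizing. That stands as a reason not to demand more patients. It does not attach the 80% to the primary outcome.

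It can also be said that an article condenses the protocol and that a separate analysis plan may name the test of proportions. That stands too, and the absence of such a test is not raised here as a fault in itself. The point rests on a power figure that the article does state, for an endpoint other than its primary one.

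Two stronger readings are tempting, and the documents support neither.

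- *That 21 per arm lacks 80% power for the primary outcome.* No non-responder rates are given, so this cannot be shown. If the 50% is carried over as percentage points, power exceeds 80% in every case checked, with a minimum of 86% by Fisher at 25% v 75%. A halving from a very high rate also passes (90% v 45%: 85%).
- *That the Sample size section contradicts the Discussion.* The Discussion describes two earlier randomised crossover studies of TXB2 inhibition by formulation, in healthy volunteers and in diabetic patients (of the latter: "It examined 40 diabetic patients in a randomized crossover design"). The Sample size section does not deny that earlier studies exist. It denies that any allows a robust estimate, which is compatible with crossover data from other populations when the present trial is a parallel comparison in stroke patients. The Discussion gives no numerical rates from either study, so they cannot be used here.

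That a null result would in fact be misread as an adequately powered negative is a risk, not a certainty.

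**Conclusion.** The sample size statement is wrong as written in one definite respect: the 80% is for a difference in an unnamed mean and does not apply to the non-responder comparison, the only primary outcome. Power for that comparison is not established. Over the rates tried it runs from 8% to 91% by Fisher exact test, and 80% is reached only with a gap of about 38 to 47 points when the lower rate is 5% to 30%.

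These figures assume 21 evaluable patients per arm, two-sided 5% and illustrative rates. Fisher's test is a choice made for this check, and the uncorrected chi-square test gives somewhat higher power. The CV limit of 0.56 to 0.58 holds only for an untransformed comparison of means with a relative 50% difference. This is a mismatch between endpoint and power statement, not a proven arithmetic error or a proven shortfall.

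**What to change.** Keep N = 42 and replace the power sentence with the detectable difference for the non-responder proportion. Name the two-proportion test and label the arm rates as assumptions. For example:

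> *With 21 patients per arm (Fisher exact test, two-sided 5%), the study has about 80% power if the non-responder rates are 10% v 52.5%, 20% v 67% or 30% v 77%, and about 26% power for 25% v 50%. These rates are assumptions. A non-significant result does not exclude smaller differences.*

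If a mean is what was powered, say instead that the 80% refers to mean TXB2 (preferably on the log scale), give the assumed SD, and state that the non-responder comparison is not powered at 80%.

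Either change costs wording only. It adds no patients, samples or visits. The price is a less favourable power statement than the present one suggests.
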